### Sample Size

This feasibility trial will recruit a total of 10 patients.

### Recruitment

As a part of their clinical management, patients with acquired calvarial defects from the neurosurgery clinic or the skull base/head and neck clinic at the PAH will be reviewed as candidates for cranial reconstruction via the Osteopore implant by the MDT. Referrals to this process will be accepted from throughout Queensland via standard pathways, and national out-of-catchment referrals will be considered for special circumstances in which the PAH has unique expertise. The specific conditions assessed may include acute and subacute pathologies (major acute fractures with bone loss, bone malignancy, etc) or chronic pathologies (osteomyelitis, osteoradionecrosis, etc).

The relevant specialties that will be involved in the MDT review and decision-making process include infectious diseases, plastic and reconstructive surgery, neurosurgery, infectious diseases, and engineering. The MDT will determine the best treatment option for each patient. Should cranial reconstruction by using an Osteopore implant be recommended by the MDT, the patient’s treating specialist will discuss the case with the coordinating principal investigator, and the extent to which the potential participant satisfies the trial’s inclusion and exclusion criteria will be determined collaboratively. Written informed consent will be obtained following the MDT’s decision and prior to the conduct of the cranioplasty. Informed consent must be completed prior to any study-related activities.

Patients will be followed up for at least 24 months from the time of initial reconstruction. Given that the PAH collectively sees around 5 patients per year with significant bone defects, the recruitment phase will take place over 2 to 3 years to recruit a total of 10 patients for the feasibility analysis.

In addition to the prospective recruitment pathway detailed above, patients who have undergone cranioplasty via the Osteopore implant may also be recruited into the study at the discretion of the sponsor and coordinating principal investigator.

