The regenerative capacity of vascularized corticoperiosteal tissue is well recognized [36,37]. It has a robust blood supply, and potential donor sites for distant transfer are plentiful [19]. For uniform scaffold vascularization, an intrinsic approach is considered key [38]. However, to date, a combined intrinsic and flap-based approach to scaffold vascularization that also exploits the innate autologous regenerative capacity of corticoperiosteal tissue for bone regeneration has not been explored. We define the coalescence of these concepts as RMAV, whereby a corticoperiosteal flap is used to vascularize scaffold intrinsically and also produce bone.

Between 2016 and 2018, we undertook a preclinical study that evaluated the concept of RMAV by using a corticoperiosteal flap from a sheep’s hind limb and a 3D-printed mPCL-TCP scaffold to reconstruct 6- and 3-cm intercalary defects of the tibia [20]. This technique was compared against existing control data sets for this animal model. Control groups were reconstructed with autologous bone grafts alone, were reconstructed with mPCL-TCP scaffolds alone, or were left unreconstructed [20]. The regenerative matching approach resulted in the enhanced volume of regenerate bone, as shown on plain x-ray and micro-CT images [20], and equivalent biomechanical torsional stiffness when compared to the approach using bone grafts alone. In December 2019, we performed a first-in-human case study of applied RMAV, wherein a 3D-printed mPCL-TCP scaffold with rhBMP-7 and vascularized corticoperiosteal flaps was used to successfully perform a reconstruction of a large calvarial defect that had failed to heal after conventional cranioplasty [39]. This work builds on our experiences with bone defect reconstructive research, and it will involve the regenerative matching technique.

Given these successes in preclinical research and our first-in-human case, we feel that the logical next step for the emerging RMAV technique should be a robust feasibility clinical trial examining the behavior of the mPCL-TCP implant and postimplantation bone healing. Once appropriate outcome measures are clearly defined, it may then be appropriate to proceed to a randomized clinical trial in which RMAV is compared to other clinical techniques for a given bone defect.

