## Methods

### Study Design

Our study will be a single-arm feasibility trial that evaluates the outcomes of using an mPCL-TCP scaffold, in conjunction with a vascularized corticoperiosteal tissue, in participants with acquired defects of the calvarial bones of the skull resulting from trauma, malignancy, or infection. The study will capture data that will be used to inform the design of future clinical trials in this area.

The mPCL-TCP scaffold that will be used in the study will be manufactured by the trial sponsor—Osteopore International Pte Ltd (Singapore). Osteopore products are made of a US Food and Drug Administration–approved polymer (K051093) called *polycaprolactone*, which is bioabsorbable, is malleable, is slow to degrade, and possesses mechanical strength that is similar to that of trabecular bone. The product will be manufactured by using 3D printing technology that is precise and allows for the customization of shape and geometry. The unique, 3D-printed, biomimetic microarchitecture of the 3D scaffolding, which is contained within Osteopore products, allows for the infiltration of cells and blood vessels, of which both play a key role in wound healing and tissue repair.

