### Analysis

All patients who are registered for the trial will be accounted for in the (intention-to-treat) analysis. For retrospectively recruited patients, all data points may not be available for all assessments, or data collection may have occurred outside of the trial-specific window (eg, CT data are available for the 9-month follow-up but are not available for the 12-month follow-up). In such cases, these subjects will not be evaluated for a particular analysis unless the number of data points required for the analysis is enough, or a trend can be extrapolated from the data that were collected outside of the trial-specified window.

A quantitative analysis that relates to the evaluation of the cost-effectiveness of this approach will not be undertaken as a part of this study, as the data set will most likely be too small to achieve statistical significance. Instead, the outcome measures that have an impact on the financial burden for treating patients will be combined with data from other similar trials that are conducted in the future, and the analysis of health economics data will be undertaken at that point.

Statistical analyses of descriptive statistics for the demographic, primary, and secondary outcomes at each time point will be conducted. A comparison analysis of the questionnaire results at each time point and a univariate Cox regression analysis of the time to weight-bearing for the affected limbs will be performed due to the small sample size. Statistical significance will be defined as *P*<.05. Data will be analyzed by using SPSS for Windows version 22 (IBM Corporation).

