### Measures for Avoiding and Limiting Bias

The study represents a high-quality clinical study in which bias will be kept to an absolute minimum. The study will be heavily controlled with the well-defined inclusion and exclusion criteria that will ensure that the number of patients with confounding features will be reduced, thereby effectively minimizing sources of selection bias and increasing the homogeneity of the cohort under investigation.

The follow-up period is 24 months. Generally, we would expect to see sufficient bone regeneration for most extensive defects by this time. Ongoing care will be provided in accordance with the recommendations of the treating surgeons and other members with relevant specialties, as appropriate.

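### Already-operated patients can enter at the joint discretion of sponsor and coordinating investigator when early outcome may be known, which conflicts with the claim that selection bias is minimized

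*Protocol article*

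**What the plan says.** The Protocol article describes a prospective route under Recruitment: review by the multidisciplinary team, a check of eligibility, then consent before the operation. It then adds a route for those "who have undergone cranioplasty via the Osteopore implant may also be recruited into the study at the discretion of the sponsor"; the same sentence gives the coordinating principal investigator a share in that decision. The Study Design section says that the scaffold "will be manufactured by the trial sponsor", so one of the two deciding parties is the manufacturer.

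The Analysis section treats the retrospectively recruited patients within the overall intention-to-treat statement. It foresees that their data may be incomplete or off schedule, with the example that "CT data are available for the 9-month follow-up but are not available for the 12-month follow-up". Such a patient is left out of a given analysis unless the data suffice or a trend can be extrapolated. No separate reporting is described.

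The section on Measures for Avoiding and Limiting Bias says that the eligibility criteria reduce confounding features, "effectively minimizing sources of selection bias and increasing the homogeneity of the cohort under investigation".

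On the intervention, Study Design says that the trial "evaluates the outcomes of using an mPCL-TCP scaffold, in conjunction with a vascularized corticoperiosteal tissue", and the first inclusion criterion asks for a defect suitable for both scaffold and flap. The sentence on already-operated patients names only the implant.

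**The concern.** Time to stable regenerated bone is a primary end point (End Points), and there is no control arm. Whoever decides on a retrospective entry may already have seen that patient's postoperative course and some of the imaging. Nothing in the rule prevents a patient who is healing well from being invited and one who lost the implant early from being passed over. With 10 patients in all, a few such choices can move the result noticeably. The Discussion intends these data as a baseline for comparing current and future implants, so a selected result would carry forward.

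A second, smaller matter is what the retrospective patients received. The protocol does not say whether the eligibility criteria, including the flap, govern this route. It also does not say how a case augmented with a growth factor would be handled.

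**Working it through.** **Inputs from the protocol.** Total sample: 10 (Sample Size). Accrual: about 5 patients a year with significant bone defects, over 2 to 3 years (Recruitment). The protocol gives no union rate, no number of retrospective patients and no basis for the sample size other than accrual.

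**The plan's own figure.** 5 × 2 = 10 and 5 × 3 = 15. The target of 10 is reproduced at full uptake over 2 years, or at 10/15 = 67% uptake over 3 years.

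**Assumptions.** Let *p* be the true union proportion (assumed 60% to 80%), *k* the number of retrospective patients among the 10, and *q* the union proportion among those chosen. The expected observed proportion is

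((10 − *k*) × *p* + *k* × *q*) / 10.

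**Only united patients added (*q* = 1).** The bias is *k*(1 − *p*)/10. For *k* = 3:

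- *p* = 0.6: (7 × 0.6 + 3)/10 = 72%
- *p* = 0.7: (7 × 0.7 + 3)/10 = 79%
- *p* = 0.8: (7 × 0.8 + 3)/10 = 86%

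Over the same range of *p*, *k* = 1 gives 64%, 73% and 82%, and *k* = 5 gives 80%, 85% and 90%.

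**Softer selection.** If the odds of being chosen are OR times as high for united patients, *q* = OR × *p* / (OR × *p* + 1 − *p*). With OR = 3 and *p* = 0.6, *q* = 1.8/2.2 = 0.818. The expected result is 62.2% for *k* = 1, (4.2 + 2.455)/10 = 66.5% for *k* = 3, and 70.9% for *k* = 5.

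**Selection unrelated to outcome.** With OR = 1, *q* = *p* and the bias is 0 for any *k*.

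**Effect on a favorable-looking result.** With *p* = 0.6, the exact binomial probability of at least 8 of 10 united is 0.167 without retrospective patients. With 3 patients entered because they had united, it becomes the probability of at least 5 of 7, which is 0.420. The threshold of 8 is only for illustration; the protocol sets none.

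**Mixing of interventions.** If 3 of 10 lacked the flap and united at an assumed 40%, against 70% with it, the pooled figure would be (7 × 0.7 + 3 × 0.4)/10 = 61%, which is 9 points too low for the combined technique. Mixing can therefore work against the selection effect.

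The value *k* = 3 is also an illustration. The protocol does not say how many of the 3 patients enrolled by December 2020 came by this route. The calculation uses the proportion united. The end point is a time, and the effect on time to union is not quantified here.

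**The case against.** Several stronger readings are tempting, and the protocol does not support them.

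- **Patients without the flap are admitted.** A reader might infer this because the sentence names only the implant. Study Setting and the prospective part of Recruitment use the same short phrase, while the hypothesis, objectives, design and first inclusion criterion all specify scaffold plus flap. The phrase may well be shorthand. What stands is that the protocol should say so for this route.
- **The manufacturer alone decides.** The discretion is shared with the coordinating principal investigator. That does not remove knowledge of outcome, but it is not sole control.
- **The consent rule is broken.** Consent is to come "prior to the conduct of the cranioplasty. Informed consent must be completed prior to any study-related activities". The timing before cranioplasty belongs to the prospective route, and the retrospective sentence is expressly an addition to it. Consent before study-related activities can still be met, because the reconstruction is described as clinical care. This is an exception, not a contradiction.
- **The December 2019 first-in-human case would qualify.** There, "a 3D-printed mPCL-TCP scaffold with rhBMP-7 and vascularized corticoperiosteal flaps was used to successfully perform a reconstruction". The Background does not say that this was the sponsor's product, nor whether the patient meets the age and MRI criteria. The case does show why growth-factor use needs a stated rule.
- **The outcome is known at entry.** No interval since surgery is given. A patient operated on very recently would fit, and a 9-month scan need not settle union. Knowledge of outcome is possible, not stated.

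It can also be said that this is a small feasibility study with largely descriptive analysis, and that analysis sets are often defined in a document not shown here. That is fair. The point, however, concerns an entry rule that the article does state and a claim about bias that does not fit it.

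**Conclusion.** The concern holds in a limited form. The protocol permits discretionary entry after surgery, shared by the manufacturer-sponsor, without a consecutive-entry rule, start date or cap, and analyzes these patients with the others. That cannot be squared with its claim to minimize selection bias and increase homogeneity.

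Upward bias in union is the likely direction, but neither its sign nor its size is fixed by the documents. For 3 retrospective patients of 10, the expected shift runs from 0 (no outcome-related selection), through about 6.5 points (odds ratio 3, true rate 60%), to 6 to 12 points if only united patients are added (true rate 80% down to 60%). All of this rests on assumed union rates and an assumed number of retrospective entrants. Whether the eligibility criteria and the flap apply to this route is unresolved, and the passages must be reconciled.

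**What to change.** 1. Define the primary analysis set as patients who consented before reconstruction and received scaffold plus corticoperiosteal flap. Continue to account for every registered patient, so that this definition does not itself hide exclusions.
2. Report retrospective patients separately and descriptively.
3. If they are to be pooled, enter every consecutive eligible case since a fixed date, regardless of outcome and without discretion, and record any growth factor used.
4. State that the scaffold-plus-flap inclusion criterion applies to both routes. For retrospective patients, also state the date at which eligibility is judged. If the exclusion for active infection were applied at postoperative entry, it would remove patients with an infected implant.
5. Reword the section on bias to describe the retrospective route and what is done about it.

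The cost is protocol wording and a flag in the database. The primary set may fall below 10, with a wider interval: the exact 95% interval is 35% to 93% for 7 of 10 united and 29% to 96% for 5 of 7. On the protocol's own accrual of 10 to 15 patients in 2 to 3 years, 10 prospective patients are just attainable, but only with uptake between 67% and 100%.

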### Intervention

Prior to deciding on a treatment pathway, medical imaging will be conducted as a part of each patient’s standard clinical management, which may include CT and/or MRI scans of the head and neck, as well as white cell–labeled, whole-body bone scans. The imaging results will inform the clinical assessment performed by the neurosurgeon or the skull base/head and neck surgeon involved in the care of the patients and inform the MDT review. Clinical notes, including medical histories, will also be generated as a part of the clinical care process of patients during their clinical management. Imaging data and clinical notes that relate to the defects among patients and are collected prior to informed consent will be made available to the study participants as a part of the informed consent process.

A description of the patient journey is summarized in Figure 1. The clinical care reconstruction will be performed at time 0. A standard clinical protocol for wound care and rehabilitation will follow. Patients may undergo a review for routine clinical assessments every 3 months following the cranioplasty until they are clinically stable, with more or less frequent follow-up visits arranged according to their clinical needs.

**Figure 1 figure1:**
[figure not shown]
Flowchart of patient journey. CT: computed tomography; MDT: multidisciplinary team; mPCL-TCP: medical-grade polycaprolactone and tricalcium phosphate; MRI: magnetic resonance imaging; WC: white cell. *see "Eligibility Criteria" section; **antibiotic therapy, as indicated by infectious disease physician consultation.

The trial-related interventions will focus on capturing defined functional outcomes and, consequently, will require the collection of data at specific time points. CT and/or MRI scans of the head and neck will be used to identify complications and establish clinical and radiological evidence of union at 1, 12, and 24 months after surgery. As performing 2 CT scans in the first year during the postoperative follow-up period is standard clinical practice, the amount of ionizing radiation to which the participants are exposed will not exceed the amount of radiation that patients typically receive during standard clinical care. Additional CT and MRI scans may be performed during the follow-up period in accordance with patients’ clinical needs.

The other research-related functional assessments will include the administration of the Quality of Life After Brain Injury (QOLIBRI) and 36-item Short Form Quality of Life (SF-36) questionnaires at prereconstruction and at 1, 12, and 24 months after surgery.

### End Points

The key primary end points for evaluation in our single-arm study are the time to the formation of stable, regenerated bone that is sufficient for protecting the brain (ie, radiographic or clinical evidence of bony union) and patient-reported outcomes. These primary end points serve as surrogate markers for satisfactory bone healing but, more importantly, are clinically useful for and relevant to the study goal and overarching purpose of the intervention. Functional outcomes are more difficult to measure reliably and are therefore secondary outcomes, which will be measured with the QOLIBRI and the SF-36 questionnaires [40]. The schedule of assessments is presented in Table 1.

**Table 1 table1:** Schedule of assessments.

			Multidisciplinary team review		Enrollment		Reconstruction		Follow-up period		
									1-month review		3-, 6-, 9-, 12-, 15-, 18-, 21-, and 24-month review
Time point^a^			−t_2_		−t_1_		0		T_1_		T_2-9_
**Enrollment**											
	Informed consent			✓^b^							
	Eligibility screen			✓							
	Demographics			✓							
	Medical history and medical review	✓		✓				✓		✓	
**Interventions**											
	Infection management			✓							
	Reconstruction					✓					
**Assessments**											
	Computed tomography of head	✓						✓		✓^c^	
	Magnetic resonance imaging	✓						✓		✓	
	White cell–labeled, whole-body bone scan	✓						✓		✓	
	Quality of Life After Brain Injury questionnaire			✓				✓		✓^c^	
	36-item Short Form Quality of Life questionnaire			✓				✓		✓^c^	

^a^“t” represents a time point prior to the intervention, and “T” represents a time point after the intervention.

^b^Denotes a clinical activity from which data may be utilized for the trial analysis.

^c^Trial-related assessment at 12 and 24 months only.

### Statistical Methods

The statistical analysis of the data will be undertaken by the Queensland Facility of Advanced Bioinformatics (QFAB). QFAB personnel will use REDCap (Research Electronic Data Capture) software (Vanderbilt University) to design and validate an electronic data capture system for use in the trial. Deidentified data will be entered into the REDCap-based electronic data capture system by a member of the research team after the coordinating principal investigator or delegate has certified each case report form (CRF). The database will contain validation ranges for each variable to minimize the chance of data entry errors. An audit trail will be created to maintain a record of the initial entries and changes made, the reasons for changes, the times and dates of entries, and the usernames of the people who made the changes. Data queries will be raised, and missing data or suspected errors will be resolved prior to locking the database and performing the analysis.

### Analysis

All patients who are registered for the trial will be accounted for in the (intention-to-treat) analysis. For retrospectively recruited patients, all data points may not be available for all assessments, or data collection may have occurred outside of the trial-specific window (eg, CT data are available for the 9-month follow-up but are not available for the 12-month follow-up). In such cases, these subjects will not be evaluated for a particular analysis unless the number of data points required for the analysis is enough, or a trend can be extrapolated from the data that were collected outside of the trial-specified window.

A quantitative analysis that relates to the evaluation of the cost-effectiveness of this approach will not be undertaken as a part of this study, as the data set will most likely be too small to achieve statistical significance. Instead, the outcome measures that have an impact on the financial burden for treating patients will be combined with data from other similar trials that are conducted in the future, and the analysis of health economics data will be undertaken at that point.

Statistical analyses of descriptive statistics for the demographic, primary, and secondary outcomes at each time point will be conducted. A comparison analysis of the questionnaire results at each time point and a univariate Cox regression analysis of the time to weight-bearing for the affected limbs will be performed due to the small sample size. Statistical significance will be defined as *P*<.05. Data will be analyzed by using SPSS for Windows version 22 (IBM Corporation).

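### P<.05 is the only inferential criterion stated for the questionnaire comparisons in 10 patients, with no power basis; estimates of within-patient change would serve the trial's purpose better

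*Protocol article*

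**What the plan says.** All references are to the Methods of the protocol article.

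- **Sample Size:** "This feasibility trial will recruit a total of 10 patients". No effect size, SD or power accompanies the number.
- **Recruitment:** the number is tied to accrual (the period is in years): "Given that the PAH collectively sees around 5 patients per year with significant bone defects, the recruitment phase will take place over 2 to 3".
- **Study Design:** the purpose is stated as "The study will capture data that will be used to inform the design of future clinical trials in this area".
- **Intervention:** QOLIBRI and SF-36 are given before reconstruction and at 1, 12 and 24 months.
- **Analysis, on costs:** no quantitative cost-effectiveness analysis will be done, since "the data set will most likely be too small to achieve statistical significance". The relevant outcome measures "will be combined with data from other similar trials that are conducted in the future".
- **Analysis, on outcomes:** descriptive statistics are planned at each time point for the demographic, primary and secondary outcomes. The section adds "A comparison analysis of the questionnaire results at each time point" and a Cox regression, gives the small sample as the reason for both, and closes with "Statistical significance will be defined as *P*<.05". Neither the test for the questionnaires nor its sidedness is named.

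**The concern.** The article recognises that 10 patients are too few for a significance verdict on one analysis, then attaches a significance threshold to another analysis of the same patients without asking the same question. No other criterion for interpreting the questionnaire comparison is stated.

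This fits poorly with a feasibility trial meant to inform later ones. Planning the next trial takes an estimate of how much scores change, how much that change varies between patients, and how uncertain both figures are. A threshold on P supplies none of these. If power is low for changes that matter, a P value above .05 carries little information, and the threshold draws attention away from the estimates that the trial can provide.

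**Working it through.** **1. Can the sample size be reproduced?** Not from a power formula, because the article gives no statistical inputs. It agrees with accrual: 5 per year × 2 years = 10, and 5 × 3 = 15. The stated 10 is the lower end.

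**2. Inputs for the check.**
- n = 10 (Sample Size), taken as all evaluable. This is the favourable case, since the Analysis section accepts that retrospectively recruited patients may lack data points. No rate is given, so no smaller n is calculated here.
- Significance level 0.05 (Analysis); two-sided is assumed.
- Test: paired t-test, prereconstruction against one later visit (assumed).
- Effect d = true mean change ÷ SD of the within-patient change. The article gives neither part, so a range is shown.

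**3. Power.** Noncentral t with 9 degrees of freedom and noncentrality d√10:

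| d | d√10 | Power |
|---|---|---|
| 0.3 | 0.95 | 14% |
| 0.5 | 1.58 | 29% |
| 0.7 | 2.21 | 51% |
| 0.8 | 2.53 | 62% |
| 1.0 | 3.16 | 80% |
| 1.2 | 3.79 | 92% |

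Power passes 50% at d = 0.69. A simulated Wilcoxon signed-rank test at n = 10 gives 28%, 60% and 79% for d = 0.5, 0.8 and 1.0, so the choice of test hardly matters. For 80% power the paired t-test would need 34 patients at d = 0.5 and 15 at d = 0.8.

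**4. Sensitivity to the definition of effect.** Suppose the change of interest is 0.5 of the SD of scores at one visit, with equal SDs at both visits and correlation r between them. Then d = 0.5/√(2(1−r)):

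| r | d | Power at n = 10 |
|---|---|---|
| 0.3 | 0.42 | 22% |
| 0.5 | 0.50 | 29% |
| 0.7 | 0.65 | 45% |
| 0.8 | 0.79 | 61% |
| 0.9 | 1.12 | 88% |

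**5. Precision of the mean change.** The 95% CI half-width is t(0.975, 9)/√10 = 2.262/3.162 = 0.72 of the observed SD of change. Equivalently, P<.05 is reached only when the observed mean change exceeds 0.72 of the observed SD of change.

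**6. Precision of the SD of change.** The 95% CI runs from √(9/19.02) = 0.69 to √(9/2.70) = 1.83 times the observed SD. For a given target difference in score, a sample size scales with the square of the SD. The planning figure is therefore known only within 0.69² = 0.47 to 1.83² = 3.3 times its estimate.

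**7. Do the planned descriptive statistics cover this?** Only in part. With SDs s₀ and s₁ at two visits, the SD of change is √(s₀² + s₁² − 2r·s₀·s₁). With equal SDs s it is s√(2(1−r)), which is 1.18s at r = 0.3 and 0.45s at r = 0.9. Means and SDs by visit do not contain r, so they do not determine the SD of change.

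**The case against.** **The two statements can stand together.** A within-patient comparison of scores can need fewer patients than a cost-effectiveness analysis. The secondary objective is only to collect data for a later cost evaluation, and those data are deferred to pooling, not discarded. This stands: a reader might see a contradiction, but the text supports only an uneven rationale.

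**Nothing says that non-significance will be reported as no change.** This also stands. A reader might infer that a worthwhile change will usually be missed and then reported as absent. The article defines a threshold and does not say how a result above it will be worded. Whether a change is usually missed depends on its size: below about 0.7 SD of the change it is missed more often than not at n = 10, while changes of 0.8 to 1.0 SD would be detected 62% to 80% of the time.

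**Descriptive statistics are planned as well.** True, and they cover the questionnaires, so the threshold is not the only output. It is still the only inferential criterion stated, and statistics by visit do not give the spread of within-patient change.

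**An article leaves such detail to the full protocol or SAP.** This is fair for confidence intervals and for the exact test, and their absence is not held against the plan. The point rests on what the article does fix: a P<.05 criterion for 10 patients, with a sample size that it ties only to accrual.

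**Conclusion.** The point holds as a modest improvement to the stated analysis. The P<.05 criterion has about 29% power for a change of 0.5 SD and reaches 80% only near 1.0 SD of the within-patient change. This assumes a two-sided paired t-test, all 10 patients evaluable, and an effect size that the article does not supply. Under those assumptions a non-significant questionnaire result would be weak evidence either way, and the criterion does not deliver what the Study Design section says the trial is for. The check does not show that the plan contradicts itself, that most worthwhile changes will be missed, or that the investigators intend to report non-significance as absence of change.

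**What to change.** In the Analysis section, for QOLIBRI and SF-36:

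- Make the main result the mean within-patient change from prereconstruction to each later visit, with its 95% CI.
- Report the SD of that change with its 95% CI (0.69 to 1.83 times the estimate if all 10 are evaluable), as a planning input for the next trial.
- Show each patient's change.
- Label any P values exploratory, and state that P≥.05 will not be read as no change.

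The word significant need not be banned. The significance sentence also governs the Cox regression in the same paragraph, so it should be reworded to make clear which analyses it covers.

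The cost is a few sentences of text. No additional data, visits or patients are needed. The sponsor gives up a confirmatory significance claim on the questionnaires.
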